## Abstract

**Background:**

Emotion-Focused Skills Training (EFST) is a newly developed manualized skill training program for parents to strengthen emotional bonds between parents and children and improve mental health outcomes in children. Results from several preliminary trials indicate that EFST can be quite effective, but more rigorous methods are needed to affirm the evidence of the program. The primary objective of this study is to compare the effectiveness of EFST to treatment as usual (TAU) in a Norwegian outpatient clinic for child and adolescent mental health. Additionally, the study will examine the basic theoretical assumption underlying EFST that increased parental emotional functioning predicts a decline in children’s mental health symptoms.

**Method:**

120 patients will be randomly assigned to either EFST or TAU. The main outcome measure is the semi-structured diagnostic interview Schedule for Affective Disorders and Schizophrenia, present and lifetime version (K-SADS-PL) scored by trained assessors administered at pretreatment and repeated after 3 months. The secondary outcome measure is the DSM-IV version of the Strength and Difficulties Questionnaire (SDQ) administered at pretreatment as well as 3, 6, and 12 months after the intervention. To examine the efficacy question, effect sizes and reliable change for each of the treatment arms will be assessed as well as symptom differences between the conditions. To examine the second aim of the study, we will examine (1) how parents relate to emotions in their children assessed by the Emotion-Related Parenting Styles (ERPS), (2) the parents’ emotion regulation capacity assessed by the Difficulties in Emotion Regulation Scale, short-form (DERS-SF), and (3) parents’ sense of self-efficacy and the strength of their relationship with the child will be assessed by the relationship with child scale (RWC) of the systemic inventory of change.

**Discussion:**

This study will provide insights into the effectiveness of EFST in improving children’s mental health and the mechanisms of change responsible for the program’s effectiveness. Impotently, this study may provide information regarding whether children’s mental health issues can be alleviated through therapeutic work provided to the parents alone.

**Trial registration:**

Clinical trials.gov Identifier: NCT04885036. First Posted on May 13, 2021. Trial status: In recruitment.

## Background

It is estimated that approximately 20% of children and adolescents experience some form of psychological distress that affects their level of functioning and quality of life and that approximately 7% are in need of professional assistance from specialist mental health care [1]. In Norway, mental health issues are estimated to cost society approximately 7 billion EURO per year [2]. Only around half of all children with mental health diagnoses will recover from their initial childhood mental health concerns by early adulthood [3]. Thus, effective, empirically supported, and cost-effective mental health programs are needed to address these issues more successfully. Today, a diversity of therapeutic approaches is offered in treating mental health difficulties among children and adolescents. Among these approaches are individual therapy [4], family therapy [5, 6], play therapy [7, 8], and group therapies [9]. While most of the approaches above have been shown to positively affect children’s and adolescents’ mental health status, many clients do not receive adequate treatment and care [10].

Parents play a key role in alleviating mental health problems in children and adolescents [11, 12]. Parental emotion awareness, emotion regulation, and response to their children’s emotions and their capacity to coach or guide children in how to recognize, understand, and regulate emotions, play a central role in the development of mental health in children [13, 14]. While the dominant approach in evidence-based parenting programs has been based on teaching behavioral strategies [5], recent findings support the importance of more emotion-focused interventions when parents and children experience emotion dysregulation [15]. Parental interventions are recognized as efficacious for the treatment of several mental health difficulties in children [5]. Even so, there is still a need to strengthen existing approaches and develop and test new interventions within this area. It is important to develop efficacious interventions when children are able and motivated to participate in therapy. However, it is also crucial to develop viable alternatives for situations when children do not wish to or are unable to participate in treatment. Emotion-Focused Skills Training (EFST) is an approach that aims to reach children and adolescents and alleviate mental health difficulties by *guiding parents to help their children recognize and cope with their emotions.* EFST was originally introduced as Emotion-Focused Family Therapy [16, 17] and has been further developed as a short-term parental skills training program (EFST). EFST is an integrative program based on principles from affective neuroscience, emotion theory, research on emotion-focused therapy [18], and humanistic person-centered therapy [19, 20].

EFST is an increasingly used treatment approach among therapists in outpatient clinics for child and adolescent mental health (i.e., BUP) in Norway. One example is the Department of Child and Adolescent Mental Health at Sorlandet Hospital (Abup) in Southern Norway, which has offered EFST to more than one hundred families during 2021. Prior studies examining the effects of EFST in community settings have demonstrated promising results, both when provided as a two-day caregiver workshop [21–23] and as a two-day workshop followed by individual sessions [24]. In a previous trial conducted by researchers affiliated with this current trial, two versions of EFST were compared in a randomized clinical dismantling study. Participants were parents of children with mental distress in a community sample. The standardized EFST protocol was compared to a psychoeducational version of EFST [24]. Results showed a significant decrease in both internalizing and externalizing symptoms, and the standard EFST protocol produced the most promising results. A weakness of the study was the absence of a comparison group other than the two EFST treatment variants. Thus, a comparison of EFST to a waitlist or active control group is necessary to determine its effectiveness.

Additionally, to our knowledge, the effect of EFST has not been thoroughly investigated in clients with more severe mental health problems and documented mental illnesses, such as those generally treated in Norwegian outpatient clinics for child and adolescent mental health. In a pilot study, members of our research team compared the effects of EFST to a group-based CBT treatment for children suffering from a clinical range of anxiety of different types (e.g., separation anxiety, social phobia, OCD). The results from the nine children included in this pilot study indicated that EFST had similar treatment effects as the CBT treatment ([name], [name], [name], [name], [name]. Emotion Focused Skills Training for Parents with Anxious Children, a Pilot Study. 2022. Manuscript in preparation.). In the present study, we intend to compare the effectiveness of EFST intervention with treatment as usual (TAU). TAU in this study is the typical family-based intervention offered at the clinic (Department of Child and Adolescent Mental Health at Sorlandet Hospital, ABUP, in Southern Norway) which has already been documented as effective [25, 26]. There are reasons to anticipate that EFST effectiveness can be comparable to TAU.

EFST is based on the theory and practice of Emotion-focused therapy (EFT), which is a model for working with adult individuals and couples, and which has gathered extensive empirical support [27–30]. EFT is a process-oriented, humanistic-experiential, transdiagnostic approach based on the assumptions that emotional difficulties result from emotions that are no longer functional in helping the individual in an adaptive way [31–33]. EFT therapists support their clients in alleviating psychological distress by developing awareness of their emotions, labeling them into words, regulating their emotions, making meaning of their emotions, and transforming maladaptive emotions developed in the context of difficult experiences early in life [34]. The primary aim of EFST is to guide parents to become effective emotion coaches for their children. It is hypothesized that enhancing parents’ emotional awareness and ability to handle emotions will enable them to better understand and meet the child’s emotional needs, thereby improving the child’s emotional difficulties and reducing mental health difficulties [12]. However, to our knowledge, this assumption is not yet empirically tested.

## Aims and research questions

Using a randomized controlled trial in routine care, we aim to compare EFST with TAU within an outpatient clinic for child and adolescent mental health (BUP), as presented in Fig. 1. We have two main hypotheses. Our first hypothesis is that the two conditions are equivalent when it comes to effectiveness. Our second hypothesis is that an increase in parents’ emotional functioning predicts a decrease in mental health symptoms for their children.

**Fig. 1 Fig1:**
[figure not shown]
Flow of participants in the study

Hence, the research questions we examine in this study are:1. How does the EFST intervention compare to TAU in effectiveness?2. Is there empirical evidence to support the EFST theory that parental increased emotional functioning can predict a decline in children’s mental health symptoms?

## Methods

### Study design

The proposed trial is a randomized controlled trial with two intervention groups. Participants are allocated into one of two groups, EFST or control group, TAU.

### Participants

Participants will be children referred to the child and adolescent mental health department at Sorlandet Hospital (Abup) in Southern Norway. As a standard procedure at the clinic, regardless of whether one takes part in a research project, all clients (i.e., children) undergo a standardized assessment of their functioning and symptoms of mental distress and developmental history. If, from the initial assessments, it is determined that the client is eligible for a family-based treatment in the family team of the clinic, the children and their parents will be invited to take part in this study. To be eligible, the following criteria must be met: a) the child meets the criteria for a mental health disorder, b) the disorder is assessed by health professionals to be related to parent or family functioning, and c) the families are motivated to work within a family-based framework to improve the suffering of their child and the relational difficulties in the family. The main researcher or the head of the family team will provide participants information about the study in age appropriate ways and go through the written consent form. After consent for participation, each family (one child with one or two parents) will be assigned randomly to one of the treatment conditions using the www.randomizer.org website. Randomization will be requested by the therapist responsible for recruitment and clinical interviews. Based on the clinic’s experience of research, an anticipated drop-out rate of 20% is reasonable [35, 36]. With 80% power, an expected effect size of 0.4, and an anticipated 20% drop-out rate, the number of clients in each condition is calculated to be 60, following a procedure described by Schönbrodt & Wagenmakers [37]. By choosing Bayesian statistics, evidence will be obtained even when the power calculations might be mis specified [38].

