### Measurements

To investigate the research questions, a combination of evaluations and scores from professionals administering the Schedule for Affective Disorders and Schizophrenia for School-Age Children–Present and Lifetime version (K-SADS PL; [41]) and self-evaluation questionnaires with solid psychometric properties will be used at the time points presented in Table 1. As shown, T0 is at pretreatment, T1 after three months, T2 after six months, and T3 after 12 months. With TAU not being a manualized intervention with a fixed length of treatment, we decided to measure the symptoms of the child 3 months after starting the program. At that time, the EFST treatment is terminated, and TAU has reached the point in treatment (if not ended) where we have reason to believe that the treatment has had an effect.

**Table 1 Tab1:** Measures and timeline of assessment

**Measures**	**T0**	**T1**	**T2**	**T3**
K-SADS	x	x		
SDQ	x	x	x	x
KINDL-R	x	x	x	x
DERS-SF	x	x	x	x
ERPS	x	x	x	x
WAI		x		
SCL-10	x	x		
RWC	x	x		

#### Measures for research question 1

To answer our first research question, *How does the EFST intervention compare to TAU in effectiveness*, we will use both a semi-structured interview and parent, teacher, and self-report measures. Our primary outcome measure is the Schedule for Affective Disorders and Schizophrenia in School-Age Children-Present and Lifetime Version (K-SADS-PL), a semi-structured diagnostic interview conducted by qualified clinicians. The interview will be conducted at T0 and T1 to investigate the presence of one or more mental health diagnoses of the children. A diagnosis will be rated as present or not as described in the interview guide [42]. K-SADS-PL is a semi-structured diagnostic interview used to evaluate current and lifetime episodes of psychopathology in children and adolescents. The measure can be used to evaluate at least 33 psychiatric disorders in children and adolescents [43]. In the proposed study, the K-SADS-PL interview will be conducted with the child and parent together. International studies suggest good validity and reliability of the K-SADS-PL [41, 44, 45], and it is validated for the Norwegian population [43].

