### Data management

An elaborate data management plan has been approved by the hospital’s research department. All data will be stored according to the rules and regulations of the hospital to ensure confidentiality of the data at all stages of the research process. All study-related information will be stored securely at the study site. All participant information will be stored in locked file cabinets in areas with limited access. Only the main researchers and one research assistant will have access to the data.

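### One therapist recruits, conducts clinical interviews and requests randomisation on an open website, so concealment is not secured and the primary-outcome rater may know the arm

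*Protocol article*

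**What the plan says.** Under Participants, each family, once consent is given, "will be assigned randomly to one of the treatment conditions using the www.randomizer.org website". The article then adds: "Randomization will be requested by the therapist responsible for recruitment and clinical interviews". Information and consent lie with other named roles: "The main researcher or the head of the family team will provide participants information about the study". One eligibility criterion rests on clinical judgement, namely that "the disorder is assessed by health professionals to be related to parent or family functioning".

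The primary outcome is the K-SADS-PL, described under Measurements as "a semi-structured diagnostic interview conducted by qualified clinicians". On timing: "The interview will be conducted at T0 and T1 to investigate the presence of one or more mental health diagnoses of the children". Each diagnosis is rated present or absent. The Abstract describes the interview as "scored by trained assessors administered at pretreatment and repeated after 3 months". Under Inclusion and exclusion criteria the same instrument establishes the child's diagnoses at entry.

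The Measurements section has child and parent interviewed jointly. Under Research conditions, the child takes part in therapy in TAU but not in EFST. Under Therapists, the EFST therapists belong to the same family team that provides TAU. The article nowhere describes the 3-month raters as blinded or as independent of recruitment and treatment.

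**The concern.** The difficulty lies in a procedure that the article states, not only in a detail it leaves out. Three tasks that are normally kept apart are given to one role: bringing families in, interviewing them and triggering the allocation.

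Two things are at stake.

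- **Entry.** On an open number generator with no stated custodian or record, a draw can be repeated or thrown away without trace. Eligibility depends partly on judgement, so there is room for such a choice to alter who enters which arm.
- **Primary outcome.** The K-SADS-PL is the only interview the article describes, so the clinical interviews in that sentence plausibly include it. If the same therapist repeats it at 3 months, a present/absent diagnosis is scored by someone who requested, and so can know, the allocation.

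Rating bias of this kind is not corrected by intention-to-treat analysis, multiple imputation, Bayesian modelling or a larger sample. The Discussion says that EFST should be offered more widely if it proves as beneficial as TAU. A masked disadvantage would therefore feed directly into practice.

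**Working it through.** **Reading the statements together**

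1. Participants: the therapist who recruits and interviews requests the randomisation, and so can learn the arm.
2. Inclusion criteria and Measurements: the K-SADS-PL serves both entry and the primary outcome, at baseline and again after allocation.
3. Measurements and Abstract: the raters are qualified clinicians or trained assessors. Both terms describe competence. Neither describes independence or blinding.
4. It follows that an arm-aware rater at 3 months is permitted by the text and nowhere excluded.
5. There is a second route to unblinding. Child and parent are interviewed together, and only TAU children have attended therapy, so a remark from the family can reveal the arm.

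**Size, by illustration**

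The article gives no figure for rating error, so there is none to reproduce. From the article: 60 per arm and 20% drop-out, hence 60 × 0.80 = 48 per arm with outcome data. Assumed: a diagnosis persists at 3 months in 50% of each arm, a fraction *m* of persisting EFST cases is coded absent, TAU is rated without error, and the arms are compared by a simple risk difference.

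Shift in the risk difference = 0.50 × *m*:

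| *m* | Shift |
|---|---|
| 10% | 0.50 × 0.10 = 5 points |
| 20% | 0.50 × 0.20 = 10 points |
| 30% | 0.50 × 0.30 = 15 points |

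95% half-width = 1.96 × √(2 × 0.5 × 0.5 / 48) = 1.96 × 0.102 = 0.20, or about 20 points. The shift is thus between one quarter and three quarters of the half-width.

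**Masking a real difference**

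Suppose true persistence is 60% in EFST and 50% in TAU, a 10-point disadvantage for EFST. Observed EFST persistence is 0.60 × (1 − *m*):

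| *m* | Observed EFST | Observed TAU | Apparent difference |
|---|---|---|---|
| 10% | 54% | 50% | +4 points |
| 20% | 48% | 50% | −2 points |
| 30% | 42% | 50% | −8 points |

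At 10% leniency more than half of the disadvantage disappears. At 20% all of it does. At 30% EFST looks better than TAU.

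**The case against.** The strongest reply is that much of this rests on silence in a condensed article, and that the one explicit sentence proves neither bias. Several parts of that reply stand.

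- A reader might infer that allocation is not concealed and that no locked sequence exists. The text does not support this. The therapist requests an assignment, after consent, and a third party may draw or hold it. If families are drawn one at a time after consent, the next allocation cannot be foreseen. What remains is the repeated or discarded draw.
- A reader might infer that this therapist also decides eligibility. The article attributes the judgement-based criterion to health professionals generally, and information and consent to the main researcher or the head of the family team.
- A reader might infer that this therapist rates the 3-month K-SADS-PL. The phrase about clinical interviews may mean the baseline assessment only, and the raters are named in the plural.
- A reader might infer that bias in either direction favours an equivalence conclusion. It does so only when it opposes a true difference. With truly equal arms, leniency toward EFST creates an apparent advantage.
- The illustration uses assumed values.

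The full protocol may contain safeguards. The article nevertheless combines the roles in so many words. If safeguards exist, that sentence misdescribes the trial and still needs correcting.

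**Conclusion.** The point holds in a limited form. The described procedure does not secure concealment, and it leaves open that the primary outcome is rated by someone who knows the arm. It does not establish that allocation was predictable or tampered with, or that the 3-month raters did know the arm.

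Under the assumptions above (50% persistence, 10–30% of persisting EFST cases coded absent, error in one arm only), the bias would be 5–15 percentage points against a half-width of about 20 points with 48 per arm. These figures show what such leniency could do. They do not estimate what occurred. Because the risk reaches the primary outcome and the remedy is mainly a reallocation of tasks, the change should be made.

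**What to change.** Recruitment is already under way, so the change can cover only the remaining families and the 3-month interviews still to be done.

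1. **Sequence.** An existing staff member who does not recruit, interview or treat should hold the sequence, made by simple randomisation or with randomly varied block sizes. Fixed blocks in an open trial run within one team could make allocations easier to guess. Each assignment is released, with a log entry, only after consent and baseline measures are recorded. The Data management section mentions one research assistant with data access. That person would serve only if confirmed to be outside those three tasks, which the article does not state.
2. **3-month K-SADS-PL.** Assign it to an existing trained assessor who neither recruited nor treats the family and is not told the arm. Ask families not to disclose it, and record the assessor's guess of arm so that residual unblinding can be measured.
3. **Reporting.** State who holds the sequence and who rates at 3 months. Report as a limitation any 3-month interviews already done by raters who knew the arm.

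The cost is some scheduling effort and a notice to the ethics committee, to which the article already undertakes to report procedural changes. Blinding will remain imperfect, because child and parent are interviewed together and the child attends therapy only in TAU.

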### Data analyses

To test our first hypothesis that the two conditions are equivalent when it comes to effectiveness, Bayesian growth curve analysis and t-tests will be used to assess the effect of the two arms as compared to each other. Independent sample t-test will be performed on the SDQ to compare the outcome of the two conditions for every five clients included in the study. If strong evidence of difference of the treatment effect is provided with few clients, the data collection can stop. To test our second hypothesis that an increase in parents’ emotional functioning predicts a decrease in mental health symptoms for their children, Bayesian growth curve analyses will be used. Bayesian analysis is preferred because it allows for the specification of models that are appropriate for the data and the capacity to provide estimates and credible intervals for any derived parameter. Additionally, when using Bayesian analysis, credible intervals are not dependent on large-N approximations (as confidence intervals used in frequentist statistical approaches), nor are credible intervals dependent on the type of test being performed (as confidence intervals do in frequentist approaches). Furthermore, Bayesian analysis gives methods for evaluating support for the null hypothesis, not just against it [66]. Moreover, it enables monitoring of data collection to see whether there is sufficient evidence to draw conclusions or if additional data is required [67]. Indeed, there is evidence that within child and adolescent mental health research, conclusions could have been made with smaller sample sizes than what was obtained in many cases [68]. The effect size of interest is the difference in treatment effect between each of the arms in the study. Effect sizes of treatments within our field vary [10, 69], with treatment effects of 0.80 regarded as good. In line with conventional procedures in meta-analyses [65], we consider a difference of 0.40 as meaningful. Based on the experience of research within the clinic, an anticipated drop-out rate of 20% is reasonable [35, 36]. Clinical significant change will be assessed using the method defined by Jacobson & Truax [54]. Missing data will be managed with multiple imputation and all analyses will be performed as intention to treat (ITT).

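### The stated 80% power for an effect of 0.4 with 60 per arm and 20% drop-out is not reproduced by the t-test the protocol names; under usual assumptions that test has about 49% to 62%

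*Protocol article*

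**What the plan says.** The sample size is set in the Participants section of the protocol article. The sentence begins "With 80% power, an expected effect size of 0.4, and an anticipated 20% drop-out rate, the number of clients in each condition"; it puts that number at 60, citing a published Bayes factor design procedure. The abstract gives the matching total: "120 patients will be randomly assigned to either EFST or TAU". Participants then adds that, because Bayesian statistics are used, "evidence will be obtained even when the power calculations might be mis specified".

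The Data analyses section says what the 0.4 refers to: "The effect size of interest is the difference in treatment effect between each of the arms in the study", and "we consider a difference of 0.40 as meaningful". For the first hypothesis it lists Bayesian growth curve analysis and t-tests. An independent-samples t-test on the SDQ is to be run after every five clients, and recruitment may stop on strong evidence of a difference. The article gives no significance level, sidedness, prior or Bayes factor threshold.

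**The concern.** A standardised difference of 0.4 between two independent groups normally needs about 100 per group for 80% power, and the plan expects about 48. The power figure is what a reader uses to judge a result that shows no clear difference. The first hypothesis is that the two treatments are equivalent, and the Discussion says EFST should be offered more widely if it proves as beneficial as TAU. If the trial has roughly even odds of missing a difference that its authors call meaningful, readers need to know that before they interpret an inconclusive result.

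**Working it through.** **Inputs from the protocol article.** Standardised between-arm difference d = 0.4 (Participants; Data analyses). 60 per arm, 120 in total (Participants; abstract). Drop-out 20% (Participants), so 60 × 0.8 = 48 evaluable per arm. Test: independent-samples t-test on the SDQ (Data analyses).

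**Assumed, because not stated.** Two-sided 5%, with one-sided levels as the range. For Bayes factors, a default Cauchy prior with scale 0.707, thresholds of 3 and 10, and looks about every five clients.

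**Step 1: try to reproduce 60 per arm.** By the normal approximation, n per arm = 2(1.960 + 0.842)² / 0.4² = 98.1, rounded up to 99. The exact t calculation gives 99.1, rounded up to 100. Allowing for drop-out, 100 / 0.8 = 125 randomised per arm. At one-sided 5% the exact figure is 78 evaluable, and 78 / 0.8 = 97.5, so 98 randomised. Neither is close to 60.

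**Step 2: power of the planned size.** The noncentrality parameter is d × √(n/2). For n = 48 it is 0.4 × √24 = 1.96, against a two-sided 5% critical value of 1.986 on 94 degrees of freedom. The signal sits almost on the critical value, so power is close to one half.

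| Evaluable per arm | Two-sided 5% | One-sided 5% | One-sided 10% |
|---|---|---|---|
| 48 | 49% | 62% | 75% |
| 60 (no drop-out) | 58% | 70% | 82% |

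At 48 per arm, 80% power (two-sided 5%) is reached at d of about 0.58.

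**Step 3: Bayes factor readings**, true d = 0.4, up to 48 per arm, looks about every five clients (simulation, 40,000 runs).

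| Prior | BF > 10 | BF > 3 |
|---|---|---|
| Default Cauchy 0.707, two-sided | 25% | 46% |
| Default Cauchy 0.707, one-sided | 35% | 60% |
| Concentrated near +0.4 | 49–52% | 75–80% |

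**Step 4: using the baseline SDQ.** With baseline–outcome correlation r, the effective difference is 0.4 / √(1 − r²). For r = 0.5, 0.6 and 0.7 this is 0.462, 0.500 and 0.560. Power at 48 per arm, two-sided 5%, is then 61%, 68% and 78%. The correlations are assumed; the article gives none.

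**Step 5: using all three post-baseline SDQ scores.** Take their mean, adjusted for baseline, with a common correlation r between all time points and a constant difference of 0.4 at each. The residual variance is (1 + 2r)/3 − r². At r = 0.3 this is 0.443, giving an effective difference of 0.4 / √0.443 = 0.60 and power of 83%. At r = 0.7 it is 0.310, giving 0.72 and 94%.

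**The case against.** The plan is Bayesian and cites a Bayes factor design procedure that is not at hand. A fixed-sample, unadjusted t-test at 5% is a stand-in, so a reader might infer that 49% is the trial's real power. The article does not support that: it states no alpha, sidedness, prior or threshold, it plans sequential looks, and it lists growth curve models beside the t-test. Nor is 49% the power for the declared primary outcome, which is diagnosis present or absent on the K-SADS-PL.

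A reader might also infer that no analysis could reach 80%, or that power under a strong-evidence Bayes factor rule is simply lower than 49%. Neither holds in general. Steps 3 and 5 show values at or above 80%, and with a prior concentrated near +0.4 the chance of BF > 10 is about the same as 49%. A one-sided 10% test with no drop-out gives 82%.

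Two further points carry weight. Multiple imputation and intention-to-treat analysis are planned, so a drop-out need not be lost at every time point. The sentence on misspecified power can be read as saying only that a Bayes factor stays interpretable at whatever size is reached, and the article mentions that monitoring can show whether more data are needed. Priors and thresholds are also the kind of detail a journal article may leave to the full plan, so their absence is not the complaint.

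What remains is that every route to 80% uses something the article does not state. BF > 3 with a prior centred on a benefit of 0.4 sits poorly with a strong-evidence rule and with a hypothesis of equivalence. The repeated-measures route needs a constant difference over 3 to 12 months and an assumed correlation. The one-sided 10% result needs zero drop-out, whereas the stated calculation includes 20%. As for missing data, even 60 complete per arm gives only 58% two-sided or 70% one-sided at 5%.

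**Conclusion.** The claim of 80% power at an effect of 0.4 with 60 per arm and 20% drop-out is not reproduced by the comparison the article names. Assuming an unadjusted t-test on 48 evaluable per arm, power is about 49% (two-sided 5%) or 62% (one-sided 5%). Reaching 80% two-sided takes about 100 evaluable per arm, roughly double the plan. With a default prior and looks about every five clients, the chance of BF > 10 is about 25% two-sided or 35% one-sided. The correct description is that the figure cannot be reproduced from the stated inputs and is well above what the named test gives; it is not shown that the trial has one true power of 49%. The sentence on evidence despite misspecification promises more than a planned sample of 120 with no stated extension rule can deliver. It needs rewording and is not a separate error. Because the power figure is relied on and cheap to correct, it should be corrected.

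**What to change.** 1. In Participants, restate the power that 60 per arm (48 evaluable) gives under the model, prior and threshold actually used. If the reference is an unadjusted two-sided 5% t-test, the statement would be about 49% for a difference of 0.40 and 80% for a difference of 0.58. If it is a Bayes factor design, give the simulated chance of reaching the threshold in use.
2. Make the three-month SDQ comparison baseline-adjusted, either by analysis of covariance or by the planned growth model with a common baseline mean. Table 1 already has the SDQ at pretreatment.
3. Reword the sentence on misspecified power to say that, with a planned sample of 120, the result may be inconclusive.

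Cost: wording and one change of analysis. No extra patients or measurements are needed. The stated power will look less favourable, and the baseline adjustment recovers part of it: 61 − 49 = 12 points at an assumed correlation of 0.5, and about 29 points (77.5% against 49.2% before rounding, so 28.3) at 0.7 when taken from the rounded figures.
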